**Intervention**

FAST-2 will be a two-group, 12-week, delayed-treatment randomized trial.

Participants will be provided with a set of four resistance bands with handles (10-40 pounds of resistance) and a standard aerobics stepper that can be adjusted to 4, 6, or 8 inches in height prior to the baseline visit. They will be instructed to perform four exercises daily, each lasting 30 seconds, and to perform as many repetitions as possible during those 30 seconds. Thirty seconds of rest will be allowed in between the exercises. Each day participants will be asked to perform push-ups, chair stands, two-arm rows, and stair stepping in the same order during each session. No written instructions will be provided, although links to videos of each exercise will be included in email communications. Participants will be instructed to perform the exercises all seven days of the week. Modifications will be provided based on the participants’ functional level and form.

Push-ups can be modified in any of the following ways: by resting on the knees instead of the toes, by placing the hands on the kitchen countertop (30 inches in most homes), by placing the hands on a set of steps (starting with the 4^th^ step from the floor) or by placing the hands on the wall. When participants are able to perform 15 repetitions of push-ups using one of the modified methods, they will beasked to progress to a higher level of difficulty (e.g., place the hands on the 3^rd^ step from the floor).

Chair stands will be performed, by default, by placing the arms across the chest, but participants can modify them if needed by placing two hands on the knees, one hand on a knee or with arms not placed across the chest. Participants will be instructed to use a standard chair with arms, without wheels and with a seat height of approximately 17 inches regardless of the height of the subject. Participants will be encouraged to progress, as they are able to do so safely, to the default position of placing their arms across the chest.

Two-arm seated band rows will be performed with the resistance band looped around the arches of the feet to allow for a full range of motion. Participants will be instructed to pull their elbows back to touch the body to complete a repetition while squeezing the shoulder blades behind together.

Participants will complete the stair stepping exercise by placing their feet up on the step reciprocally and then stepping backwards down in the same fashion. All participants will start on the 4-inch step until they can rise fully on the step with both feet six times in 30 seconds. They will be then instructed to increase the step height to 6 inches and later to 8 inches.

To increase safety, participants will be instructed to place the chair on carpet or against a sturdy object like a wall. For the stair stepping exercise, participants will be instructed to place the stair stepper in the corner of a room, so they can touch the wall if they feel unsteady.

### Coaching

At baseline and at weeks 2, 4 and 8, each participant will complete a one-on-one Zoom audio-video coaching session led by a research staff member with expertise in exercise and health psychology with the goal of improving each participant’s personal performance records. Each coaching session will last 10-20 minutes, depending on the participants’ instructional needs. The coach will begin each session by asking the participant a question designed to build rapport (i.e., “small talk”). Next, the coach will review the self-reported adherence and performance data of participants, congratulating them on any personal records and positive performance trends. The coach will emphasize to the participants the importance of moving as rapidly as possible (without sacrificing form) to pursue a standardized goal of increasing chair stands and stair steps, by four and two repetitions, respectively over the course of the 12-week intervention. The same goal will be communicated by the coach to all participants. The stated rationale of this goal is to improve walking ability, as all participants have reported difficulty walking at baseline. Before beginning the exercises, the participants will orient their camera so that the entire body will be visible by the coach. During each session, the coach will passively observe the participant complete the entire workout. The coach will ask each participant to complete the workout normally, as if they are not being observed. Upon completing the 4-minute exercise session, the coaches will provide feedback and correction (if necessary) relating to exercise form. Where form correction is necessary, the coach will demonstrate the proper movement and confirm understanding by viewing the participant perform the corrected exercise. Modifications and progression methods will be suggested and discussed. For example, once a participant can complete 15 push-ups with their hands on a kitchen countertop, the coach will encourage the participant to progress to push-ups with their hands on the 4^th^ step of a staircase (if available in the home of the participant). Safety will be emphasized during each session; coaches will encourage participants to place the stepper in a corner (to allow them to regain their balance, if needed) and to do chair stands on a carpeted floor, so the chairs will not slide. The coach will end each session by answering any questions.

### Self-monitoring, feedback, and messaging

Each participant will receive an email reminder every morning to complete the daily workout along with a link to a REDCap survey to report their performance on the four exercises (number of push-ups, chair stands, rows and steps on the stepper), whether they used exercise modifications, and their perception of exertion during the workout. Emails will include links to videos of each exercise. Every other week, participants will receive a separate email summarizing their performance and adherence and recognizing their new personal best performance.

## Delayed intervention control

Participants assigned to the delayed intervention control group will continue care as usual. Following the completion of the 12-week follow-up, participants in the delayed group will begin 12 weeks of physical activity intervention with a one-on-one audio-video Zoom coaching session occurring during the initial first week. At that time, the information given to the physical activity treatment intervention group regarding the daily exercise will be given to the delayed group.

**Measures**

**Primary Outcome Measures**

**Functional Performance Measures**

The participants in both groups will complete three functional performance measures while being observed by a trained researcher over Zoom at baseline, week 6 and week 12 (The Five-Times Sit-to-Stand (FTSTS) test, part of the Short Performance Physical Battery(SPPB)), the One-Legged Stance Test (OLST) and the 30 second chair stand test. As with the coaching sessions, the participants will orient their camera so that the entire body will be visible to the researcher

**Five-Times Sit-to-Stand (FTSTS) test**

Participants will be instructed to sit in and fully rise from a chair five times as quickly as possible, without using their arms for support. The test which will be timed using a stopwatch will end when the participant’s body touches the chair following the fifth repetition.

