**Inclusion and Exclusion Criteria**

**Inclusion Criteria**

1. Age 65 and older
2. Difficulty with walking
3. Providers must provide consent for their patient
4. Access to the internet
5. Must have a camera on computer, tablet, or smartphone
6. Fluent in English

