**30 second chair stand test**

Participants will be instructed to sit in and fully rise from a chair as many times as they can in 30 seconds.

The OLST will be performed after the FTSTS and before the 30 second chair stand test, to reduce lower extremity fatigue.

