## Statistical analysis

Summary statistics (e.g., mean and standard deviation (SD) for continuous variables; frequency and proportion for categorical variables) will be reported for participant baseline characteristics. Baseline differences between randomly assigned participants will be evaluated with two-sample t-tests and Fisher’s exact tests. Changes in the primary outcome measures over 12 weeks will be evaluated at the group level using linear mixed-effect models to analyze change over time and the Group x Time interaction. The analysis will employ an intention-to-treat approach, with missing data addressed through mixed-effects modeling in the longitudinal data analysis framework. A two-sided *p*-value of less than or equal to .05 will be considered statistically significant.

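### The FTSTS has no recorded result for participants who cannot rise unaided, and the 30-second chair stand has no arm rule

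*Protocol*

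**What the plan says.** The Primary Study Endpoints table lists both chair-rise tests, each measured at baseline, week 6 and week 12.

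- **FTSTS.** Participants are told to "sit in and fully rise from a chair five times as quickly as possible, without using their arms for support". Timing stops when the body "touches the chair following the fifth repetition". The section gives no maximum time and no score or code for failure to finish.
- **30-second chair stand test.** Participants are told to "sit in and fully rise from a chair as many times as they can in 30 seconds". Arm position and arm use are not mentioned.
- **Who can enrol.** Inclusion requires "Difficulty with walking". The nearest exclusion is a general inability to exercise. No criterion requires an unaided chair rise.
- **Training (Intervention section).** The daily chair stand may be modified by "placing two hands on the knees, one hand on a knee or with arms not placed across the chest". Participants are encouraged to progress to arms crossed when they can do so safely.
- **Raters.** Assessors are unblinded (Randomization and blinding). A blinded coder settles disagreements over repetition counts (Daily exercise performance).
- **Analysis.** The Statistical analysis section plans linear mixed models with a Group x Time interaction, by intention to treat, with "missing data addressed through mixed-effects modeling in the longitudinal data analysis framework".

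**The concern.** In the FTSTS, a missing time can itself be a result. Someone who tries and cannot complete five unaided rises has performed worse than everyone with a time, yet the protocol provides no way to say so. If the field is left blank, the mixed model treats that person as similar to participants with the same observed data who did finish. If training works, fewer treated participants than controls stay unable. The weakest controls then drop out of the comparison, while newly able treated participants enter with slow times. Both pull the estimate toward no effect.

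The 30-second test raises a separate question. A participant who cannot rise can still score 0, so inability need not create a missing value. However, a rise with hands on the knees may or may not be counted. During the 12 weeks only the intervention group trains toward arms crossed, so arm use in the test could change between visits differently in the two groups. The blinded coder has no criterion for deciding such cases. This test is also the stated basis of the sample size.

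**Working it through.** **1. The plan's own figure.** Inputs from Sample size determination: d = 0.60, two-sided 0.05, 80% power, 20% attrition. Per group, n = 2(1.960 + 0.842)² / 0.60² = 2 × 7.85 / 0.36 = 43.6, so 44 per group and 88 in total; 88 / 0.80 = 110. The plan's figures reproduce, and this point does not change them. With a t-test, 44 per group gives 79.5% power, so there is no slack.

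**2. Effect seen when inability leaves a blank.** The share unable is not in the protocol, so every value of q below is an assumption. Baseline ability b is standard normal. Week-12 ability is ρb + √(1 − ρ²)·e + 0.60 × group, with e standard normal. A score is absent below the threshold Φ⁻¹(q), so a share q of controls is unable. The baseline-adjusted group effect among participants with both scores, from a large simulation, is:

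| Controls unable (q) | ρ = 0.5 | ρ = 0.7 | ρ = 0.85 |
|---|---|---|---|
| 5% | 0.55 | 0.56 | 0.58 |
| 10% | 0.51 | 0.54 | 0.57 |
| 20% | 0.46 | 0.51 | 0.55 |
| 30% | 0.42 | 0.48 | 0.53 |

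At week 12 the treated share unable is about 1%, 3%, 7% and 13% respectively. That imbalance is what moves the estimate.

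**3. Numbers lost.** Keep d at 0.60, recruit 55 per group, lose 20% to attrition, and lose a further share q in each group: n = 55 × 0.80 × (1 − q).

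| q | n per group | t-test power |
|---|---|---|
| 0% | 44.0 | 79.5% |
| 5% | 41.8 | 77.4% |
| 10% | 39.6 | 75.1% |
| 20% | 35.2 | 69.9% |
| 30% | 30.8 | 63.9% |

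This is rough. It removes equal shares from both groups and ignores the partial data that a mixed model keeps.

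**4. Closer to the planned model.** A simulation of the Group x Time model with 44 per group compared FTSTS times, blank when unable, with a rate (5 divided by seconds) scored 0 when unable. With 5% unable the mean z was 2.7 for times and 3.0 for the rate. With 13.5% unable it was 2.5 and 2.8. The ratios are 2.7 / 3.0 = 0.90 and 2.5 / 2.8 = 0.89, a loss of about a tenth.

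**5. How much comes from the scoring.** Assume a rate with control mean 0.36 and SD 0.10 stands per second, a shift of 0.06 (d = 0.06 / 0.10 = 0.60), and inability below 0.25 (a time above 5 / 0.25 = 20 s). About 13.5% of controls are then unable. A week-12 comparison without baseline gives d = 0.51 for times in completers, 0.52 for the rate in completers, and 0.56 for the rate with unable = 0. Most of the gain comes from counting the unable, and little from the change of unit.

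**6. The 30-second test.** No arithmetic applies. The FTSTS section forbids arm support, the 30-second section is silent, and the training exercise allows hands on the knees. The adjudication rule says who decides a disputed count but not what counts as a rise.

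**The case against.** The strongest reply is that silence is not a decision. The protocol never says that inability is left blank, and it does not use the term missing at random. A scoring rule could sit in an SAP or test manual that is not shown, and the protocol describes the FTSTS as part of an established battery. This stands for the FTSTS score: the consequence above follows from the protocol as written and would disappear if a score were fixed elsewhere. It does not dispose of the arm rule. Arm position and the recording of arm use belong to test administration, and analysis cannot recover them if they were never noted.

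The training modifications also apply to a daily exercise, not to the tests, and one of them (arms simply not crossed) is not hand support. They show that participants who need support are expected, not how many.

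Three stronger readings are tempting but not supported:

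- A reader might compare raw week-12 FTSTS means and infer that newly able, slow participants wipe out most of the benefit. The planned analysis is a Group x Time mixed model. A participant with no earlier time has much of a slow result absorbed as a between-person difference, so the distortion is far smaller.
- A reader might infer that the 30-second test mis-scores the weakest. The text shows only ambiguity, since 0 is an available score.
- A reader might infer that treated participants will take a harder test at week 12. Nothing says that the test follows the training position. It is a possibility that the missing rule leaves open.

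**Conclusion.** The point holds in a limited form. The protocol provides no FTSTS result for participants who attempt the test and cannot complete five unaided rises, although it foreseeably enrols some. As written, those absences go to a model whose assumption they violate. The likely direction is toward no effect, provided that training works and more controls than treated participants remain unable. The likely size is modest: about a tenth of the test statistic under the planned type of model with an assumed 5% or 13.5% unable. In the illustrative baseline-adjusted analysis, 0.60 SD is seen as 0.58 to 0.42 SD over an assumed 5% to 30%. If almost everyone can rise unaided, the FTSTS effect vanishes.

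For the 30-second test the finding is lack of standardisation in a primary endpoint. Neither the size nor the direction of any bias can be derived from the protocol.

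**What to change.** **30-second chair stand.** State one arm rule, identical at baseline, week 6 and week 12. Say that an attempt with no valid rise scores 0, record any arm use, and give the blinded coder the same criterion.

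**FTSTS.** Record attempted-but-unable as its own category, separate from missing, and include it as the worst result. Two workable forms are a rate of 5 divided by seconds with unable = 0, or a worst-rank analysis. Either could be the main analysis or a prespecified sensitivity analysis. Leave as missing only tests not attempted for non-physical reasons.

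**Cost.** A line in the test script, a checkbox on the form and one sentence in the analysis section. The sample size does not change. The downside is some zeros or ties, which fit a linear model less neatly, and a less familiar unit if the rate is used; FTSTS times can still be reported descriptively.

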**One-Legged Stance Test (OLST)**

Subjects will be instructed to start with a comfortable base of support, with both eyes open and arms by their side and then stand unassisted on the right leg. The OLST will be measured from the time that the left foot is lifted from the floor to when it touches the ground or the other leg).

**30 second chair stand test**

Participants will be instructed to sit in and fully rise from a chair as many times as they can in 30 seconds.

The OLST will be performed after the FTSTS and before the 30 second chair stand test, to reduce lower extremity fatigue.

**Daily exercise performance**

Participants will enter their push-up, chair stand, row and step-up exercise repetitions, whether they used exercise modifications, and how difficult they felt the workout was using a survey sent daily through REDCap.

Videos will be reviewed weekly by a blinded secondary coder to measure quality and safety control for the exercises performed. All timed outcome measure performances will be immediately recorded during the Zoom session at the conclusion of each functional performance measure and re-evaluated offline by a blinded reviewer. Discrepancies in recorded times that are greater than one second will be replaced with the time recorded by the secondary reviewer. If discrepancies in recorded times are less than 1 second, the average of the two values will be used. If there is a disagreement on the number of repetitions performed between the blinded secondary coder and the unblinded research staff member conducting the exercise session, the blinded staff member will provide the final adjudication.

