**Primary Study Endpoints**

| **Measure** | **Timing** |
| --- | --- |
| Five-Times Sit-to-Stand (FTSTS) test | Baseline, week 6 and week 12 |
| One-Legged Stance Test (OLST) | Baseline, week 6 and week 12 |
| 30 second chair test | Baseline, week 6 and week 12 |
| Exercise daily performance | Daily for 12 weeks |

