## Study Procedures

## Randomization and blinding

Participants will be randomized through REDCap using stratified assignment based on biological sex and age (65-72 and 73+) to maintain equal representation of older vs. younger males and females in each group. Once randomized, patients will be informed of their assigned condition, and their study visits will be scheduled. Both participants and the research staff who conduct the assessments will not be blinded to the participants’ treatment assignments. Secondary coders that review videos weekly to assess quality and for safety control will be blinded.

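### Daily exercise performance is a primary endpoint, but the survey items the protocol names omit step height and push-up level, both of which rise during the trial, so step and push-up counts are not comparable over time

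*Protocol*

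**What the plan says.** The Protocol's Primary Study Endpoints table includes "Exercise daily performance", collected daily for 12 weeks. Statistical analysis evaluates change in the primary outcome measures over those 12 weeks.

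Three sections describe what the daily REDCap survey collects:

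- Daily exercise performance: "Participants will enter their push-up, chair stand, row and step-up exercise repetitions, whether they used exercise modifications", and how hard the workout felt.
- Self-monitoring, feedback, and messaging: the four counts, modification use and perceived exertion.
- Adherence and retention: performance, modification use and difficulty level.

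The Intervention section sets the progression. For stepping: "All participants will start on the 4-inch step until they can rise fully on the step with both feet six times in 30 seconds". Then: "They will be then instructed to increase the step height to 6 inches and later to 8 inches". For push-ups, a harder form is requested "When participants are able to perform 15 repetitions of push-ups using one of the modified methods". The Coaching section gives the example of moving from a kitchen countertop to the fourth stair.

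On video, Daily exercise performance says: "Videos will be reviewed weekly by a blinded secondary coder to measure quality and safety control for the exercises performed". It also lets the blinded coder decide "If there is a disagreement on the number of repetitions performed between the blinded secondary coder and the unblinded research staff member".

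**The concern.** A repetition is a stable unit only if the task stays the same. Here the protocol makes the task harder because the participant has improved, and a harder task can lower the count. A series of daily step or push-up counts then mixes repetitions at different loads, and the named survey items do not say which load applied on which day.

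Two things are at stake. The first is the 12-week trend in a listed primary endpoint, which would tend to understate improvement for these two exercises. The second is the feedback drawn from the same counts: a participant who moves to a harder level may stop setting personal bests in the fortnightly e-mail at the point where recognition is due.

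An analysis plan cannot fully repair this afterwards. It can stratify or adjust by level only if level was collected.

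**Working it through.** **The plan's own figures.** The protocol gives no planned size for this endpoint. Its one calculation, in Sample size determination, reproduces: n per group = 2 × (1.960 + 0.842)² / 0.60² = 43.6, rounded up to 44, so 88 in total; 88 / (1 − 0.20) = 110. It does not use the daily counts, so this point leaves it unchanged.

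**Named items against progression rules.**

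| Exercise | What the protocol changes | Does a named survey item show it? |
|---|---|---|
| Stair stepping | Height 4, then 6, then 8 inches | No. Heights are not described as modifications |
| Push-ups | Form made harder at 15 repetitions | Only on the move to the unmodified form. Countertop, fourth stair and third stair are all modified |
| Chair stands | Encouragement towards arms across the chest | Largely, through the modification item |
| Rows | No progression rule stated | Not at issue |

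**Stepping, illustrated.** Inputs: the threshold of 6 rises and the heights 4, 6 and 8 inches, from Intervention. Yardstick (an assumption): total rise in 30 seconds = repetitions × height.

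- At the threshold: 6 × 4 = 24 inches.
- A later entry of 5 is logged as 5/6 − 1 = −17%, whatever the height.
- In rise, that entry is 5 × 4 = 20 inches (20/24 − 1 = −17%), 5 × 6 = 30 inches (30/24 − 1 = +25%) or 5 × 8 = 40 inches (40/24 − 1 = +67%).

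How far the count falls on moving up is unknown. If cadence stays constant, it does not fall (0%). If total rise stays constant, it falls to 24/6 = 4 at 6 inches (−33%) or 24/8 = 3 at 8 inches (−50%). Both ends are assumptions.

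The coaching goal of two more steps has the same problem. Starting from 6, it means 8 rises at 4 inches, or 32 inches; the same rise needs 32/6 = 5.3 repetitions at 6 inches or 32/8 = 4 at 8 inches.

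**Push-ups.** After a move made at 15 repetitions, any entry from 1 to 14 is logged as a fall. Its size in load terms cannot be computed, because the protocol gives no load per level.

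**What can be inferred.** If the rules are followed, a participant who has never logged 6 steps is still on the 4-inch step. A fall just after reaching 6 steps or 15 push-ups suggests a move, but day-to-day variation or delayed compliance could look the same. The move from 6 to 8 inches has no stated trigger.

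**What observation could add.** There are 12 × 7 = 84 prescribed sessions. Coaches watch 4 (baseline and weeks 2, 4 and 8), or 4/84 = 4.8%. The protocol does not say which sessions are filmed for the weekly review. As an assumed range, this is the 4 coached sessions, one a week (12/84 = 14.3%) or all 84 (100%). In no case does the text say that level is written down.

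**The case against.** The strongest reply is that the REDCap form itself is not shown and may hold more fields than the one-sentence summaries mention. That is fair as a caution. However, three descriptions agree, and none mentions height or level. If the form already has these fields, stating so closes the point.

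A second reply is that the difficulty level named in Adherence and retention could mean push-up level, since Intervention also speaks of difficulty when it describes harder push-ups. This is possible but less plausible: the two parallel descriptions give perceived exertion and felt difficulty in that place.

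A third reply is that the triggers, the modification item and the coaches' direct view carry information. This stands in part. A reader might infer that falling counts can never be told apart from progression; the protocol does not support that. Some moves can be guessed from the count series, a move to unmodified push-ups would be flagged, and a coach watching the workout would see the level and would be unlikely to mistake it for decline. What remains is that the inference is incomplete and unrecorded.

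A fourth reply is that the consequence is small. It is indeed limited. Controls have usual care and do not do the daily exercises during the 12 weeks, so these counts cannot supply a randomised contrast. That bounds the damage, but a listed primary endpoint should still be interpretable within the arm that provides it.

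**Conclusion.** The point holds in a limited form. With the data the protocol says it collects, step and push-up counts are not comparable across a change of level, and a flat or falling count cannot reliably be separated from progression. The effect lies in the within-intervention-arm trend for two of four exercises, mainly towards understating improvement, and in the personal-best e-mails.

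The size cannot be fixed from the documents. The illustration, in which the same logged −17% stands for anything from −17% to +67%, rests on total rise as the yardstick and on an example entry of 5. The conclusion also assumes that the named items describe the survey completely.

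A reader might go further and infer that the trial's efficacy comparison is compromised. The documents do not support that. The Five-Times Sit-to-Stand, the One-Legged Stance Test, the 30 second chair stand test, their between-group comparison and the sample size are all unaffected. The change is worth making because it is cheap and the missing information cannot be fully recovered later.

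**What to change.** Add two pick-list fields to the daily REDCap survey: step height (4, 6 or 8 inches) and push-up level. Name them in Daily exercise performance and in Self-monitoring, feedback, and messaging. Have the coach confirm both at the sessions already scheduled. Summarise step and push-up counts by level, or together with the level reached. In the e-mails, count a move to a harder level as a personal best.

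The cost is two fields, one item on the coach's form and a changed e-mail rule. There are two downsides. The daily survey becomes slightly longer, and a session counts towards adherence only if the survey is completed. If the fields are pre-filled from the previous day to save effort, some entries may go stale after a move, and the coach's check would catch these only in part.

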### Criteria for removal from study

Participants may be from the study if they become injured and cannot exercise or if they are asked by their Primary Care Provider to suspend exercise. The Principal Investigator reserves the right to remove a participant from the study for any reason, based on their discretion, particularly a belief that continued participation exposes them to unnecessary risk. Also, participants have the right to withdraw themselves at any time and halt all study-related activities permanently.

Other withdrawal criteria include: unwillingness to follow protocol during visits, unwillingness to complete study visits, and/or return of equipment to study staff, withdrawal of consent by the participant, development of a new medical problem that would exclude them from the study.

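### The protocol describes no systematic collection of falls, injuries or new pain in either arm, and incidental reports would not be comparable between arms

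*Protocol*

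**What the plan says.** Only the Protocol is at hand. On this point it says the following.

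- **Exposure.** Under Intervention: "Participants will be instructed to perform the exercises all seven days of the week". The intervention lasts 12 weeks.
- **Observed workouts.** Under Coaching: "At baseline and at weeks 2, 4 and 8, each participant will complete a one-on-one Zoom audio-video coaching session", and in each of these "the coach will passively observe the participant complete the entire workout".
- **Test visits.** Under Functional Performance Measures, both groups do the tests "while being observed by a trained researcher over Zoom at baseline, week 6 and week 12".
- **Daily survey.** Self-monitoring, feedback, and messaging lists the repetition counts, then "whether they used exercise modifications, and their perception of exertion during the workout". Daily exercise performance and Adherence and retention describe the same content, with difficulty in place of exertion.
- **Video review.** Randomization and blinding has "Secondary coders that review videos weekly to assess quality and for safety control will be blinded", and Daily exercise performance has "Videos will be reviewed weekly by a blinded secondary coder to measure quality and safety control for the exercises performed". Neither says which videos are meant.
- **Prevention.** The eligibility screening sends PAR-Q answers to the primary care provider for permission. The exclusion criteria remove people with chest pain or a heart condition. The Intervention section tells participants where to place the chair and stepper. Coaches correct form and stress safety.
- **Action on injury.** Participants may be removed "if they become injured and cannot exercise", or when their provider asks them to suspend exercise.
- **Lapsed participants.** Under Adherence and retention, three or more missed days lead to phone and email contact whose stated aim is re-engagement. Attempts end after 14 days without a response.
- **Controls.** They receive usual care for the 12 weeks. No coaching or daily survey is described for them in that period.

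**The concern.** The measures above either prevent harm or respond to it. None of them records it. No harm appears in the primary or secondary endpoint tables, among the measures, or in the described content of the survey.

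This matters because of who is exercising and how. Participants are older adults with difficulty walking, urged to move as fast as good form allows, and one exercise has them step backwards off a raised platform. The Protocol itself treats unsteadiness as a risk, since it places the stepper in a corner so that a wall is within reach.

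Two things are at stake. An injury at home may reach staff late, or only as a run of missing surveys. And at the end the trial could report benefit by arm without a harm count by arm that means the same thing in both.

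**Working it through.** The Protocol gives no figure on this point, so there is none to reproduce. The check is a count of contacts and a comparison of sections.

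**1. Share of workouts observed** (Intervention; Coaching)

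- Prescribed: 12 weeks × 7 days = 84 per participant.
- Observed by a coach: baseline and weeks 2, 4 and 8 = 4.
- Share: 4/84 = 4.8%. This is an upper figure. If the baseline session is not one of the 84, it is 3/84 = 3.6%.
- Adding the week 6 and week 12 test visits gives at most 6 Zoom contact days, 6/84 = 7.1%.
- Assuming half of the 110 recruits are in the intervention arm (55): 55 × 84 = 4,620 prescribed workouts, 55 × 4 = 220 observed, 4,400 not observed.

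**2. What the survey would show.** Its content is described in three sections. All three give performance, modification use and exertion or difficulty. None mentions a fall, an injury or pain. A session counts as completed only if the survey is filled in, so a person who is hurt and stops exercising would first be visible as missed sessions.

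**3. How an injury would become known.** The removal criteria presuppose that staff know of it. No section says who asks, when, or where the answer is recorded. The contact after missed days has no stated question about harm.

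**4. Channels by arm, baseline to week 12**

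| Channel | Intervention | Control |
| --- | --- | --- |
| Coaching after baseline (weeks 2, 4, 8) | 3 | 0 |
| Test visits (weeks 6, 12) | 2 | 2 |
| Scheduled live contacts in total | 5 | 2 |
| Daily survey | up to 84 | none described |
| Contact after missed sessions | yes | does not apply |

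With no common question, a fall has more chances to be mentioned in the intervention arm. A higher count there could reflect more contact, and equal counts could hide a real difference.

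**5. What asking would buy.** If everyone in an arm of n is asked and nobody reports an event, the one-sided 95% upper bound on the proportion affected is 1 − 0.05^(1/n). For n = 55 this is 5.3%, and for n = 44 (the evaluable number per group under Sample size determination) 6.6%. If participants are not asked, an absence of reports supports no such bound.

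**The case against.** The best case on the other side is that safety has been thought about, that injuries have several ways of coming to light, and that the survey instrument itself is not shown, so it may contain an item that the prose omits. The trial also lists no safety endpoint, and its hypothesis concerns function only.

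Much of this stands, and it rules out several stronger readings that a reader might infer:

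- *Video review is the only safety control.* It is not. Provider permission, exclusions, equipment placement, coaching and removal criteria are all stated.
- *The Protocol claims weekly video of every workout.* It does not. The same paragraph goes on to Zoom recordings and to staff conducting the session, so weekly review may simply mean that accrued Zoom recordings are reviewed each week. The source of the videos is unclear, but that is ambiguity and not a contradiction.
- *Harms go uncaptured, or an injury shows only as a lapse.* Coaching, test visits, contact after missed days or a provider's request could each bring one to light.
- *About 95% of exposure carries no safety information, and controls have none.* The 4.8% measures live observation only. Injuries can be reported afterwards, exertion is reported daily, and controls are seen at weeks 6 and 12.

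What does not stand is the inference that these routes suffice. They are incidental and unequal between arms. An unseen survey item may exist, but three descriptions of the content omit it, and controls are not described as receiving the survey. Nor can this be left to an SAP: what participants are asked is settled in the protocol, and an analysis plan cannot recover answers never collected.

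**Conclusion.** The point holds in a limited form: the text describes no systematic ascertainment of harm in either arm, and the incidental routes favour detection in the intervention arm, with five scheduled live contacts after baseline against two. At least 80 of 84 prescribed workouts per participant are not observed by a coach. The removal criteria depend on information that no described procedure gathers.

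This rests on two assumptions: that the survey contains what the Protocol says and no more, and that no other procedure for collecting harms exists in material not shown. If either fails, the remedy reduces to stating that procedure and making it equal across arms. The sample size (88, recruiting up to 110) and the efficacy analysis are unaffected. The change should be made, but nothing here invalidates the design.

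**What to change.** 1. Add one yes/no item to the existing daily REDCap survey: any fall, injury or new pain since the last report, with free text. Its purpose is early detection, not comparison between arms.
2. At the existing week 6 and week 12 Zoom tests, ask the same scripted question of both arms with the same fixed look-back, for example since the previous test visit.
3. Base the harm counts by arm on those two visits only, and report how many participants were asked in each arm, because those who have left will not be covered. With arms of this size the counts are descriptive.
4. In Randomization and blinding and in Daily exercise performance, state which videos are reviewed. If they are the Zoom sessions, say so.

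The cost is one survey item, two scripted questions and a clarification of wording, with no new visit. The small downside is a slightly longer survey and some follow-up of reported events.
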